**Baseline characteristics**					
N/A	Maternal demographics	X			
**Primary objectives**					
Acceptability	Program acceptability			X	X
	Qualitative interview**			X	X
Satisfaction	Participant satisfaction			X	X
	Qualitative interview**			X	X
Home visitor-participant relationship	Working alliance inventory: 1. Client WAI 2. Home visitor WAI		X	X	X
Retention	Participant tracking information collected throughout the duration of the pilot study				
Adherence					
**Secondary objectives**					
Maternal substance use	Alcohol, Smoking and Substance Involvement Screening Test	X	X	X	X
Maternal depression	Edinburgh Postnatal Depression Scale	X	X	X	X
Parenting feeding practices	Child Feeding Assessment		X	X	X
Maternal parental knowledge	Parent Knowledge Assessment	X	X	X	X
Child development	Ages and Stages: Social Emotional - 2*		X	X	X
	Ages and Stages Questionnaire, 3rd Edition*		X	X	X
Quality of life	EURO-QOL	X	X	X	X
Maternal self-efficacy	Parenting Locus of Control			X	X
Maternal stress	Perceived Stress Scale 4	X	X	X	X
Substance abuse/domestic violence risk	Institute for Health and Recovery Integrated Screening Tool	X	X	X	X
Client priority outcomes	Top problems	X	X	X	X

*These measures will not be administered as part of the Care4 data collection platform, as they are licensed by ITC of MI external to the Care4 platform

**Qualitative interviews will only be conducted with intervention participants at midpoint and endpoint

Participants receive a gift card upon completion of the following assessment timepoints: baseline, 2 months, 6 months, and 12 months postpartum. Total possible remuneration for participants in the study is $70 in gift cards.

From study midpoint until the endpoint of the study timeline, home visitors will be asked to participate in focus group discussions (FGDs) by video conference. Each site will participate in up to 10 short FGDs. FGDs will be designed to take approximately 30 min to complete and will be scheduled during regular study site meetings. They will be recorded with permission and transcribed verbatim. Home visitors receive a $15 gift card upon completion of each FGD. Total possible remuneration for home visitors is $150 in gift cards.

### Outcomes

Selected measures are being used to assess implementation and clinical outcomes (Table 2).

#### Primary outcomes

Our primary outcomes of interest include participant acceptability, satisfaction, quality of relationship between home visitor and client, retention, and adherence. Acceptability is measured from the perspective of the participant using a 15-item scale [16] administered at study midpoint and endpoint. Satisfaction is captured through a 34-item questionnaire used in the Family Spirit trials and adapted specifically for this study and administered at midpoint (around 6 months postpartum) and endpoint. All Precision Family Spirit participants are invited to participate in a short qualitative interview to further explore acceptability and satisfaction using an 11-item interview guide. In addition, we will explore home visitor acceptability and satisfaction through focus group discussions that follow a 9-item interview guide. The quality of the relationship between home visitor and client is captured using the short version of the Working Alliance Inventory (WAI) administered to both participant and home visitor. The WAI measures three domains of the relationship: goal alignment, task alignment, and bond. Retention is measured by comparing the number of participants who drop out in each study arm. Adherence is measured by comparing the percentage of retained participants in each study arm who completed their lessons as prescribed.

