## Methods/design

### Trial design

This study uses a two-arm pilot randomized Hybrid Type 3 design [14]. Four Family Spirit home visiting sites from the Inter-Tribal Council of Michigan (ITC of MI) were selected based on comparability and randomized using a 1:1 allocation to provide either Standard Family Spirit or Precision Family Spirit to their clients. Sites were matched based on annual volume of clients served and geographic similarity (i.e., urban vs. rural) (Fig. 1).

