### Participants

Our target population for recruitment is women who are *either* pregnant or have a baby no older than 2 months of age. All study participants must be at least 14 years of age and already enrolled in the Family Spirit program in their community. Since 2013, the CAIH and the ITC of MI have partnered on implementing the Family Spirit model across participating tribal communities. The ITC of MI has a strong infrastructure to support the incorporation of a research study into their existing home visiting programming.

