### Randomization

Participating ITC of MI sites were randomized to use the Precision Family Spirit implementation strategy or Standard Family Spirit (control condition). Randomization occurred before recruitment began at the site level. The four sites were selected based on comparability of annual volume of clients served and geographic similarity (i.e., urban vs. rural). Once sites were matched, the study team flipped a coin to decide which sites would be assigned to each study arm. Participants are blind to whether they receive Standard Family Spirit or Precision Family Spirit as randomization occurs at the site-level. Thus, all participants at each site receive the same version of Family Spirit (standard or precision).

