### Standard Family Spirit

Mothers at the control sites receive Family Spirit as usual, per existing ITC of MI program policies and procedures. In the standard of care, families receive regular home visits, delivered in the same sequence until 3 years postpartum (63 lessons total). Because the duration of enrollment for this pilot study is from pregnancy to 12 months postpartum, Standard Family Spirit participants should receive 47 lessons total. Home visitors at Standard Family Spirit sites use the Care4 platform to track their clients. They receive notifications about high depression scores, risk of self-harm, and potential domestic violence issues, but they do not receive notifications about other risk categories (first-time mom, substance use, nutrition, sexual and reproductive health) that would inform tailoring sequences in the Precision Family Spirit implementation approach. Details on the rationale for selecting these risk categories have been described elsewhere [9, 16].

In both arms of the study, home visitors provide referrals and connections to community agencies and services as needed. Existing procedures are in place to link participants to assistance that is available in their area. Home visitors often act as navigators and advocates for the families they serve. In addition, participant transportation to and from doctor and clinic appointments is common and will continue for enrolled participants in each arm.

The study team recognizes that differences may be small regarding number of prescribed lessons between Precision Family Spirit and Standard Family Spirit participants, but implementation outcomes may be potentially detectable because we are measuring program participant acceptability, satisfaction, quality of relationship between home visitor and client, retention, and adherence.

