### Data collection time points

Participant assessments include maternal self-reports using Care4 and an interview (Table 2). Self-reports are conducted in participants’ homes, another private location, or via text/email on an as needed basis. Data is recorded on either a tablet, computer, or paper. If data is collected on paper, the home visitor enters the data into Care4 upon her return to the office. In some cases, assessments are conducted via text or email, once the home visitor discusses on a case by case basis with the study management team. For example, if a home visit is cut short, assessments may be completed post-visit by the participant. A secure link is sent via text or email with instructions on how to complete and submit. All participants will be assessed at four timepoints: baseline, 2 months, 6 months, and 12 months postpartum. Each assessment timepoint is estimated to take participants between 30 min and 1 h to complete. In an effort to mitigate participant time burden, home visitors complete assessments with participants during already-scheduled visits, by scheduling a separate visit, or by emailing or sending links to participants via SMS to complete the forms on their own time. Precision Family Spirit participants may also be asked to participate in a phone interview at study midpoint (between 4.5 and 6.5 months postpartum) and study endpoint (between 11 and 13 months postpartum), adding an additional 15–20 min of participant time burden for each interview completed. The purpose of these interviews is to further contextualize data being collected as part of the quantitative assessment.

**Table 2 Tab2:** List of hybrid trial objectives and evaluation measures

Pilot trial objectives	Instrument	Timepoint			
		Baseline	2 months postpartum	6 months postpartum	12 months postpartum

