#### Primary aim analysis

As this is a pilot study, most data analysis will be exploratory, but based on best practices in the field to analyze clinical trial data. We will conduct an “intent to treat” analysis as the primary analysis approach. Baseline demographic characteristics will be explored to examine comparability between the groups. For continuous measures, we will explore average scores and distributions at each time point. To test for effects, we will use mixed-effects regression models (MRMs) to estimate average differences between outcomes on the standard vs. precision approaches using the scores on the acceptability, participant satisfaction, and home visitor-client relationship assessments. Specifically, we will add a dichotomous indicator for participants receiving the precision approach compared to the standard approach and examine the interaction of that dichotomous indicator with the change in outcome measure. The MRMs will include random effects at the individual and site levels to account for multiple time points within an individual and clustering by site. We will also examine the differences in proportion of participants who dropped out and who received 50% dosage using mixed effects logistic regression models accounting for clustering by site. For all analyses, we will report both unadjusted and adjusted analyses (adjustment based on differences in baseline demographics between the two groups at the *p <* 0.1 level). For all qualitative data, we will use thematic analysis to analyze interview transcripts using Dedoose software [37]. As transcripts are reviewed, “memos” will be generated to document initial impressions of topics and themes. Segments of transcripts will then be assigned codes based on a priori (i.e., from the interview guide) or emergent themes (i.e., open coding) [38].

All analyses for the secondary outcomes will be done on an exploratory basis only.

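### Retention is a yes/no dropout outcome with no allowance for time at risk, although mothers enter anywhere from pregnancy to 2 months postpartum; an imbalance in entry stage could bias the arm comparison

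*Protocol article*

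**What the plan says.** **Outcome.** In the Primary outcomes section: "Retention is measured by comparing the number of participants who drop out in each study arm". No start point, common window or person-time measure is attached.

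**Model.** In the Primary aim analysis section: "We will also examine the differences in proportion of participants who dropped out and who received 50% dosage using mixed effects logistic regression models", with clustering by site. The comparison is therefore of proportions, reported unadjusted and adjusted. Adjustment is for baseline demographics that differ between arms at p < 0.1. Stage of pregnancy or infant age at entry is not named.

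**Entry.** Under Participants, a woman must be pregnant "or have a baby no older than 2 months of age", and "already enrolled in the Family Spirit program in their community". No gestational limit is given.

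**End of follow-up.** The Standard Family Spirit section says "the duration of enrollment for this pilot study is from pregnancy to 12 months postpartum". The assessments after baseline are anchored to delivery: "All participants will be assessed at four timepoints: baseline, 2 months, 6 months, and 12 months postpartum".

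**Allocation.** The four sites were "randomized using a 1:1 allocation to provide either Standard Family Spirit or Precision Family Spirit to their clients", so there are two per arm. Matching was on annual client volume and urban or rural setting. "Randomization occurred before recruitment began at the site level".

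**The concern.** Follow-up stops at a fixed infant age but starts whenever the mother joins. A mother who consents in early pregnancy has many more months in which to be counted as a dropout than one who consents at 8 weeks postpartum. The outcome and the model treat the two alike.

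Two things are at stake.

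- **The arm comparison.** Retention is a primary outcome and the problem the precision strategy was built to address. If one arm's sites recruit more postpartum mothers, that arm will look better retained with no difference in engagement. Site matching does not address entry timing, and a site random effect handles clustering without removing a difference in entry mix between arms. The p < 0.1 rule may or may not catch it, since entry stage is not listed as a demographic and the test has little power with 60 mothers.
- **The planning figure.** The pilot is meant to supply sample size inputs. A single dropout proportion pooled over exposures of about 10 months and up to about 18 months or more is hard to carry to a trial with a different entry mix. This holds even if the arms are balanced.

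**Working it through.** **1. The plan's own figure.** The sample size section states that a 35% difference in retention is detectable with N = 60, α = 0.05 and 80% power. The base rate and sidedness are not stated. A two-sided comparison of two proportions with pooled variance, 30 per arm (dropout is the outcome, so no deduction for attrition) and no clustering gives:

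| Retention compared | Power |
|---|---|
| 30% vs 65% | 0.79 |
| 40% vs 75% | 0.80 |
| 50% vs 85% | 0.84 |

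The figure reproduces at mid-range base rates and serves as a yardstick below.

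**2. Time at risk.** Assumptions: delivery at 40 weeks, 12 months = 52.18 weeks, 2 months = 8.70 weeks.

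- Entry at gestational week g: (40 − g) + 52.18 weeks
- Entry at 2 months postpartum: 52.18 − 8.70 = 43.48 weeks

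| Entry week g (assumed) | Weeks at risk | Ratio to 43.48 |
|---|---|---|
| 12 | 80.18 | 1.84 |
| 20 | 72.18 | 1.66 |
| 28 | 64.18 | 1.48 |

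In months, entry m months before delivery gives (12 + m)/10. For m = 7.5 this is 1.95, and for m = 9, the theoretical limit, 2.1. The realistic range is about 1.5 to 2.

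**3. Dropout by entry stage.** Assume a constant weekly hazard h, the same in both arms, so that dropout = 1 − exp(−h × weeks). Solve h so that an equal mix of prenatal and postpartum entrants gives 30% overall (the plan's attrition allowance), or 50% (the Background's one-year figure for other programmes).

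| g | Overall | Prenatal entrants | Postpartum entrants | Gap (points) |
|---|---|---|---|---|
| 12 | 30% | 37.5% | 22.5% | 15.0 |
| 20 | 30% | 36.3% | 23.8% | 12.5 |
| 28 | 30% | 34.8% | 25.2% | 9.6 |
| 12 | 50% | 60.5% | 39.5% | 20.9 |
| 28 | 50% | 56.7% | 43.3% | 13.4 |

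**4. Spurious arm difference with no true effect.** Difference = (prenatal share in one arm − prenatal share in the other) × gap.

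- Equal mix: 0 × gap = 0.
- 80% vs 40% prenatal (assumed), 30% dropout: 0.4 × 15.0 = 6.0, 0.4 × 12.5 = 5.0, 0.4 × 9.6 = 3.9 points.
- 80% vs 40%, 50% dropout: 0.4 × 20.9 = 8.4 down to 0.4 × 13.4 = 5.4 points.
- Complete separation of entry stage by arm: the full gap, about 10 to 15 points at 30% dropout.

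**5. Scale.** Six points of 30 mothers is 1.8 mothers; 3.9 points is 1.2. The standard error of the arm difference at 30% dropout with 30 per arm is √(2 × 0.3 × 0.7 / 30) = 0.118, about 12 points before clustering. Expected dropouts in total: 0.30 × 60 = 18.

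**The case against.** The strongest case against runs as follows. This is an exploratory pilot, and the Limitations section already concedes that four sites are unlikely to give fully comparable arms. The size rests on stacked assumptions: a constant hazard, all late entrants at exactly 2 months, all early entrants at one gestational week, and a chosen 80/40 split. The resulting 4 to 6 points is half or less of the sampling standard error and far below the 35-point detectable difference. An endpoint at a fixed infant age is also defensible, since the Background quotes its retention benchmark at one year postpartum.

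Most of that limits the size of the point without removing it. The bias is unlikely to create a significant result; it would distort an estimate. The fixed infant-age endpoint can stay. What it needs beside it is an analysis that uses each mother's time at risk. Nor is this detail left to an analysis plan, because the article states both the outcome and the model.

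Three stronger readings are tempting but unsupported:

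- *Entry mix is confounded with arm.* The article gives no entry mix by arm or site. Imbalance is possible, not shown.
- *Late entrants are a selected group of survivors and early entrants are not.* Every mother must already be in the programme at entry, so prior retention applies to both groups.
- *Retention should be redefined as staying from 2 to 12 months postpartum among mothers still enrolled at 2 months.* That conditions on an event after randomization and discards the early dropouts the strategy aims to prevent. It also sits badly with the stated intent-to-treat analysis.

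**Conclusion.** The point holds as a weakness of the outcome and model, not as a demonstrated bias. Time at risk differs between mothers by about 1.5- to 2-fold, depending on an earliest entry the article does not state. Neither the outcome, the model, the matching nor the adjustment rule deals with this explicitly. If entry stage is unbalanced between arms, the retention difference is biased: about 4 to 6 points for an assumed 80% versus 40% prenatal mix under a constant hazard and 30% dropout, and zero for an equal mix. A hazard that changes with time since consent or with infant age would alter these figures. Separately, and whatever the balance, the pooled dropout rate mixes exposure lengths and is a weaker planning input for the full trial than it need be. The matter is worth correcting because retention is a primary outcome and the change is small.

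**What to change.** 1. Keep all mothers in the intent-to-treat retention comparison as planned.
2. Beside it, add an analysis of time from consent to dropout, censored at 12 months postpartum.
3. In the adjusted retention model, include stage at consent as a prespecified covariate whatever its baseline p-value. Use a single term: pregnant versus postpartum, or weeks relative to delivery.
4. Report entry stage by arm, and dropout by entry stage, so that readers can judge imbalance and the full trial can be planned for its own entry mix.
5. Use retention among mothers still enrolled at 2 months postpartum at most as a supplementary description.

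**Cost.** Wording and analysis only; recruitment and delivery do not change. Pregnancy stage or infant age must already be established to judge eligibility. The time analysis also needs consent and dropout dates. Table 2 refers to participant tracking information without listing its fields, so that both dates are held is an assumption to confirm. The statistical price is one more model term with only about 18 expected dropouts at 30%, which is why the covariate should stay a single term.

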#### Secondary outcomes

As part of the Hybrid Type 3 approach, we also monitor specific maternal behavioral and mental health outcomes and child physical and social-emotional development outcomes.

Maternal substance use is measured at all assessment timepoints (baseline, 2, 6, and 12 months postpartum) using an adapted version of the World Health Organization’s validated Alcohol, Smoking and Substance Involvement Screening Test (ASSIST) [23, 24]. The ASSIST screens for all levels of problem or risky substance use (alcohol, illegal drugs, prescription drugs, and tobacco use). A risk score is provided for each substance, and scores are grouped into low, moderate, or high risk.

Maternal depression is measured at all timepoints (baseline, 2, 6, and 12 months postpartum) using the validated Edinburgh Postnatal Depression Scale (EPDS) [25]. The EPDS is a 10-item self-rating scale that was specifically designed for women who are pregnant or have just had a baby. However, it has also been shown to be an effective measure for general depression in the larger population [26].

Parent feeding practices are measured at 2, 6, and 12 months postpartum using an assessment developed by the study team. It is adapted from a child feeding assessment used in two other CAIH randomized trials in Southwest Native American communities [27, 28]. The assessment will be used to assess feeding practices, introduction of complementary feeding and introduction of sugar sweetened beverages among newborns and infants.

Maternal parenting knowledge is measured at all timepoints (baseline, 2, 6, and 12 months postpartum) using a 10-item assessment developed by the study team and tied to core Family Spirit curriculum content.

Other maternal outcomes are measured at all timepoints (baseline, 2, 6, and 12 months postpartum) using short screening tools or measures: overall quality of life is measured using the EuroQol [29], maternal self-efficacy is measured using the Parental Locus of Control scale [30], parental stress is measured using the Perceived Stress Scale 4 [31], substance abuse/domestic violence risk is measured using the Institute for Health and Recovery Integrated Screening Tool [32], and client priority outcomes are measured using the Top Problems measure [33]. Each measure included in this assessment is valid and reliable, with some having been shortened through a previous secondary data analysis using Item Response Theory Methods [34].

Child development is measured using the parent-report, validated Ages & Stages Questionnaire (ASQ-3) [35] and Ages & Stages Questionnaire: Social-Emotional, Second Edition (ASQ:SE-2) [36]. The ASQ-3 is used to monitor all five domains of child development and screen children for developmental delays during the first 5 years of life. The ASQ:SE-2 focuses on social-emotional development of the child. The ITC of MI uses the ASQ-3 and ASQ:SE-2 as part of ongoing programmatic data collection. The CAIH will export sum scores at 2, 6, and 12 months postpartum for both assessments to use in data analysis.

#### Quality assurance

To ensure quality of participant consent procedures, all study staff have been certified to consent participants. Home visitors received initial in-person training on informed consent. Post-training, they had to demonstrate mastery of a full informed consent procedure with their supervisor prior to being certified. Program supervisors used a checklist to certify home visitors at their site.

Quality assurance of lesson delivery for both study arms occurs according to existing ITC of MI procedures. All home visitors are required to pass knowledge tests on each lesson prior to administering them to clients. Further, they must complete role plays and achieve a total average score of at least 3 out of 4 on a quality assurance form administered by a supervisor or program manager. To ensure ongoing high quality of lesson delivery, home visit observations are conducted at least biannually and ideally quarterly. For home visitors with at least 5 years of experience implementing Family Spirit, they are observed annually or more frequently if desired by the home visitor. Home visitors participating in this pilot trial are, in general, experienced in delivering Standard Family Spirit*.* Of 13 trained home visitors, 8 (62%) have at least 5 years of experience as Family Spirit certified home visitors. Further, 11 (85%) have at least 3 years of experience. All home visitors have been trained for at least a year before this pilot trial launched.

